#### **7.4 Withdrawal of individual subjects**

Subjects can leave the study at any time for any reason if they wish to do so without any consequences. The investigator can decide to withdraw a subject from the study for urgent medical reasons.

Patients in the dialysis groups (nocturnal hemodialysis, conventional hemodialysis, peritoneal dialysis) that receive a renal transplant during the study period are asked to undergo a MSCT, pulse wave velocity measurement and laboratory investigation within one month after transplantation. This enables us to assess the primary and secondary endpoint, albeit after a shorter period of time than intended.

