A second question that is unanswered so far, is the pathophysiology of the vascular calcification in ESRD patients. In ESRD, serum is oversaturated with calcium and phosphorus, and in vitro precipitation would occur with the present calcium and phosphorus concentrations. Extracellular calcium-regulatory proteins, such as matrix gla protein (MGP), osteoprotegerin and human fetuin-A, are potent inhibitors of calcium-phosphorus precipitation. Animals lacking these proteins die at young age due to arterial calcifications and vessel ruptures. The serum concentration of fetuin-A is diminished in ESRD, and rises after a renal transplant. Fetuin-A-deficiency is an inflammation-related mortality risk factor and the possible missing link between chronic inflammation and high incidence of cardiovascular events in dialysis patients. However, contradictory reports describe the course of fetuin-A deficiency in renal insufficiency and diabetic nephropathy. Regarding MGP, an inverse relation between undercarboxylated MGP and aortic augmentation index, a marker of vascular stiffness, was found, suggesting that low MGP levels are a marker of active calcification.

Therefore this study aims to study non-classical risk factors in patients with ESRD, such as the calcium-regulatory proteins and inflammatory parameters. We expect that patients with advanced age, long period on dialysis, a high calcium phosphate product, increased inflammation markers and deficiency of calcification inhibitors will show the highest progression of coronary calcification. How these factors interact with the treatment modalities under study, remains to be established.

The primary endpoint of this study is the change in coronary calcification score, visualized by multi-slice CT scanning. With this technique, the amount of calcification in coronary arteries can be quantified during 3 heartbeats (i.e. in about 10 seconds) with radiation exposure less than a conventional CT-scan. The burden of this technique is therefore minimal for the patient.

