### **4.4 Sample size calculation**

The effects of the different modalities of renal replacement therapy on arterial calcification are analyzed with linear regression, after transformation of calcium scores. The effects of risk

factors for calcification, including inflammation parameters and calcification inhibitors are analyzed in a multivariate model. The mean ( $\pm$ SD) coronary calcification score in ESRD patients is 2370 ( $\pm$  352). The multislice CT-scan is extensively validated in our institute. At this level of calcification the variation between independent measurements is less than 10%. Therefore we can demonstrate an increase or decrease in calcification score of 15%, in 4 subpopulations of 22 patients with ESRD, with a type I error probability for a two sided test of 0.05 and a power of 0.90 [formula: " $N = (2(Z_{\alpha} + Z_{\beta})^2 \cdot sd) / (0.15 \cdot \text{mean})$ " where N = number of patients per group,  $Z_{\alpha} = 1.96$ ,  $Z_{\beta} = 1.28$ ,  $S = 3.52$ , mean = 2370]. To account for a dropout of patients by renal transplantation, switch to a different treatment modality, refusal of further participation or death we intend to include 40-55 patients per group – depending on the dropout, aiming to obtain complete study data in 22 patients per group.

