#### 7.6 Follow-up of patients withdrawn from treatment

After withdrawal, follow-up is performed according to the study protocol as far as possible, as depicted in the following diagram, with different examples:

[figure not shown]

Example 1: when a patient treated with conventional hemodialysis receives a renal transplant after 1 ½ years, for this patient the study will end at 1 ½ years. Now all measurements, including calcium score and coronary MSCT and PWV will be done at 1 ½ years after inclusion, and within one month after the renal transplant.

Example 2: when a patient who is treated with peritoneal dialysis develops claustrophobic symptoms, follow-up is completed according to the study protocol, except for the MSCT.

Example 3: when a patient who is treated with a renal transplant and renal function deteriorates to a GFR less than 30 ml/min, follow-up will be done as planned apart from the coronary MSCT, because contrast medium cannot be given.

Example 4: when a patient treated with conventional hemodialysis receives a renal transplant before 1 ½ years, the patient is asked to participate again in the study; new baseline measurements will be performed, but the coronary MSCT will not be done at inclusion, nor after 3 years. In this case the total radiation exposure will not exceed than the exposure in the original study (maximum of 11.3 mSv).

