### **9.2 Univariate analysis**

The relation between each independent variable (demographic data, calcium-phosphate parameters, inflammation markers and calcification inhibitors), and primary outcomes will be determined with univariate linear regression analysis. The relationship between these independent variables and secondary outcomes (change in coronary calcification score, change in pulse wave velocity) will be determined with univariate linear regression analysis. Because the relative change in calcification score can be independent from the initial absolute calcification score, the results will be corrected for initial calcification score.

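### Dialysis patients who are transplanted contribute a change in calcification over less than 3 years, and neither the endpoint nor the stated models account for the length of the interval

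*Protocol*

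**What the plan says.** - **Exit scan.** Protocol 7.4 covers patients in the three dialysis groups who are transplanted during the study. They are asked to have a CT scan, a pulse wave velocity measurement and laboratory tests within one month after transplantation. The stated purpose is: "This enables us to assess the primary and secondary endpoint, albeit after a shorter period of time than intended".
- **Worked example.** Example 1 in 7.6 takes a haemodialysis patient transplanted at 1½ years and says "for this patient the study will end at" that point, with all measurements made then.
- **Early transplants.** Under 7.5, patients transplanted within 6 months of inclusion move to the transplant group with no additional measurements. Those transplanted between 6 and 18 months are invited to join the transplant group as new participants.
- **Endpoint.** Section 7.1.1 names the change in coronary calcification score, with no interval and no annual unit. The design section sets follow-up at 3 years, with calcium scans at inclusion and at 1, 2 and 3 years.
- **Models.** Section 9.1 gives multinomial logistic regression in three categories for progression, and unspecified regression analyses for comparing groups. Section 9.2 gives linear regression, in which "the results will be corrected for initial calcification score". Section 9.3 adds a list of covariates (age, gender, weight, blood pressure, medication, laboratory values and others). Follow-up time is in none of them.

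**The concern.** A change measured over 1½ years is not comparable with one measured over 3 years, and here the short intervals do not fall evenly across groups. Only nocturnal haemodialysis, conventional haemodialysis and peritoneal dialysis patients can leave by transplantation and have the exit scan counted. Such exits are expected: the summary and section 4.4 both give transplantation as a cause of loss, and the two control groups are restricted to patients who are or could be eligible for the waiting list (4.1).

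If calcification progresses, a shorter interval gives a smaller change or a lower progression category. The dialysis groups would then look better than they are, in the comparison that the primary objective is about.

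A smaller matter is that exit pulse wave velocity and laboratory values are taken after transplantation. The introduction says of fetuin-A that its serum level is reduced in ESRD "and rises after a renal transplant", so a post-transplant value does not describe the dialysis period.

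**Working it through.** **1. The plan's own figure.** Section 4.4 states that "we can demonstrate an increase or decrease in calcification score of 15%, in 4 subpopulations of 22 patients with ESRD". The design values are two-sided alpha 0.05 and 90% power. Inputs: mean 2370, SD 352, difference 0.15 × 2370 = 355.5.

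- n = 2 × (1.96 + 1.28)² × (352 / 355.5)² = 20.6, rounded up to 21 per group. An exact two-sample t-test has power 0.891 with 21 per group and 0.905 with 22, so 22 is reproduced.
- The formula legend prints S = 3.52. That value would give 0.2 patients, so it is a misprint of 352.
- 352 is the SD of the score, not of the change, so any power figure built on it is only illustrative.

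**2. Loss to follow-up.** The 25% loss in the summary needs 22 / 0.75 = 29.3, so 30 enrolled. Enrolling 40 to 55 to keep 22 implies losses of 1 − 22/40 = 45% to 1 − 22/55 = 60%. These are all-cause figures. No transplant rate is given, so 25%, 45% and 60% serve below only as assumed scenarios.

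**3. Shortening of follow-up.** Assumptions: constant exit hazard, all exits by transplantation, linear progression, and patients transplanted before 6 months removed from the dialysis groups (7.5).

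- Hazard: h = −ln(1 − f) / 3, where f is the share exiting within 3 years.
- Mean follow-up of those remaining: m = 0.5 + (1 − exp(−2.5h)) / h.
- Observed share of the true 3-year change: k = m / 3.
- Share of the true transplant-versus-dialysis difference retained: (k − r) / (1 − r), where r is the transplant progression rate divided by the dialysis rate, here assumed to be 0.5.

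| f | h | m (years) | k | dialysis change too small by | difference retained |
|---|---|---|---|---|---|
| 25% | 0.096 | 2.72 | 0.908 | 9% | 82% |
| 45% | 0.199 | 2.47 | 0.823 | 18% | 65% |
| 60% | 0.305 | 2.25 | 0.749 | 25% | 50% |

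**4. Cross-check with a simpler model.** If a share f of endpoint values is taken at time t, the observed mean change is 1 − f(1 − t/3) of the true one. With f = 25% and times spread evenly from 0.5 to 3 years (mean 1.75), this is 1 − 0.25 × (1 − 1.75/3) = 0.896, a shortfall of 10.4%. Over f = 10% to 45% and t = 2.5 to 0.5 years, the shortfall runs from 1.7% to 37.5%.

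**5. Illustration on the design difference.** Suppose the true 3-year progression is 30% on conventional dialysis and 15% after transplantation. With the factor 0.896, the observed difference is 30 × 0.8958 − 15 = 11.9 points instead of 15. On the plan's SD with 22 per group (normal approximation), power falls from 0.92 to 0.76.

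**6. Nocturnal versus conventional haemodialysis.** Use the same evenly spread times, true progression of 30% on conventional and 15% on nocturnal haemodialysis, and a true difference of 15 points.

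- 25% transplanted in both groups: 13.4 points observed.
- 10% in nocturnal, 25% in conventional: 12.5 points.
- 25% in nocturnal, 10% in conventional: 15.3 points.

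The contrast can shrink or grow, so its bias has no fixed direction.

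**7. Effect of using change per year.** Dividing each change by its own interval returns the ratio to 1.00 under linear progression.

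**The case against.** The strongest reply is that the protocol nowhere says the short change is treated as a 3-year change. A reader might infer that from the missing time term, but 7.4 openly acknowledges the shorter period, the summary speaks of a progression rate, and a statistical analysis plan that is not shown could annualise. This stands against any claim that a wrong method is written down. It does not remove the problem: the protocol accepts the short change as its primary endpoint and names models and covariates that cannot allow for unequal intervals, so a plan that annualised would add something section 9 lacks.

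Other stronger readings also fail:

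- **That the models adjust only for initial score.** They do not; 9.3 has a covariate list. The point is that follow-up time is not on it.
- **That the contrast would reverse.** In the formula above this needs r to exceed k, that is, transplant patients progressing at more than about 0.91, 0.82 or 0.75 of the dialysis rate in the three scenarios. The documents give no ground for assuming that.
- **That every early transplant shortens dialysis follow-up.** Section 7.5 moves those before 6 months to the transplant group, so they add no short dialysis change. Their only baseline scan precedes transplantation, however, so up to 6 months of dialysis progression is counted in the transplant group. If dialysis progression is the faster, this acts in the same direction and is not in the figures above.
- **That laboratory associations are spoiled.** Baseline and yearly samples exist before transplantation, and nothing makes the exit sample the predictor. This is a caution rather than a demonstrated error.

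It is also fair that the 45% and 60% scenarios overstate transplantation. Death, refusal and change of modality count in the planned loss, and 7.4 provides the exit scan only for transplantation.

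**Conclusion.** The concern holds in this form: a shortened change is accepted as the primary endpoint in the dialysis groups only, and neither the endpoint definition nor the stated models contain time. If progression is positive, following the text understates dialysis progression and works against the transplant benefit named in the primary objective. For nocturnal versus conventional dialysis, the effect depends on the two transplant rates.

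Under the assumptions in the working, the dialysis change is about 9% too small at 25% exits, with about 82% of the true difference retained. The 45% and 60% scenarios (18% and 25% too small; 65% and 50% retained) are upper limits. Transplant shares and timing, linearity and the halved transplant rate are all assumed. The direction does not depend on the scenario chosen, but the size does. For a study planned around a 15% difference, even the mildest of the three scenarios warrants a correction before analysis.

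**What to change.** - **Endpoint and model (7.1.1 and 9).** Define progression as change per year on the transformed score, by actual scan date. One suitable analysis is a mixed model of all scans (0, 1, 2 and 3 years and the exit scan), with modality-by-time as the effect and dialysis follow-up ended at transplantation. A random-slope model is one option among several; the essential part is that time enters.
- **Transplants before 6 months.** Reconcile 7.4, which asks every transplanted dialysis patient for an exit scan, with 7.5, which moves this subgroup without further measurements. State how a baseline scan made before transplantation is used.
- **Re-entry at 6 to 18 months.** State how the analysis accounts for patients who then appear in two cohorts.
- **Exit pulse wave velocity and laboratory values.** Do not use values taken after transplantation as dialysis-phase values; use the last ones before it.

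The cost is revised wording, a little more analysis work, and an assumption of roughly linear progression on the transformed scale. No additional scans are needed.

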### **Study design:**

Prospective observational cohort study, comparing 4 cohorts with a follow-up of 3 years; each cohort exists of 40-55 patients to account for a 25% lost-to-follow-up-rate (e.g. by renal transplantation in the 3 dialysis groups, or by mortality).

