## **9. STATISTICAL ANALYSIS**

### **9.1 Descriptive statistics**

The population characteristics are described with a categorical or continuous output, as appropriate.

The primary endpoint, coronary artery calcification score, is a continuous variable with a skewed distribution, and will be presented with its median and ranges. Progression of calcification score will be analyzed with multinomial logistic regression, dividing the coronary artery calcification score in three categories. The same goes for pulse wave velocity of the aorta and iliac arteries.

The calcification score of the different groups will be compared by regression analyses.

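### Calcification changes cut short by transplantation may enter the primary analysis beside 3-year changes, in the dialysis cohorts only, with no time term in the endpoint or the models

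*Protocol*

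**What the plan says.** Section 7.4 asks dialysis patients who are transplanted during the study to have a CT, pulse wave velocity measurement and laboratory tests within a month of the transplant. It then states: "This enables us to assess the primary and secondary endpoint, albeit after a shorter period of time than intended". Section 7.6, Example 1 applies this to a conventional hemodialysis patient transplanted after 18 months: "for this patient the study will end at 1 ½ years", with all closing measurements done then.

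Section 7.1.1 defines the primary endpoint as a change in coronary calcification score, without a unit of time. The Summary adds only that it is taken per patient. Section 9.1 says "Progression of calcification score will be analyzed with multinomial logistic regression", using three categories, and has the cohorts compared by regression. Section 9.2 corrects for the initial score, and 9.3 lists demographic, clinical and medication covariates. None of these mentions the interval between scans. The Rationale in the Summary, by contrast, states the hypothesis in terms of a progression rate.

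Section 4.4 enlarges the cohorts "To account for a dropout of patients by renal transplantation", modality switch, refusal or death, and aims for complete data in 22 patients per group. Under 7.5 and 7.6 (Example 4), patients transplanted between 6 and 18 months are asked to re-enter in the transplant cohort with a new baseline. Those transplanted within 6 months are moved to that cohort without extra investigations.

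**The concern.** A change over 18 months and a change over 36 months are different quantities if calcification accumulates, and Section 10.4 says that on conventional dialysis it does so fast. The protocol calls both the primary endpoint and gives the analysis no means of telling them apart.

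The shortening depends on cohort. A dialysis patient's interval can end at transplantation, and no corresponding early closing scan is described for the transplant cohort. Such exits are to be expected: Section 4.1 limits the conventional hemodialysis and peritoneal dialysis cohorts to patients who are, or could be, eligible for the transplant waiting list. It states no such limit for nocturnal hemodialysis, so exit rates may also differ among the dialysis cohorts.

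At stake is the primary objective. The transplant contrast would be biased against the study's own hypothesis, and the nocturnal contrast would depend partly on transplant rates.

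**Working it through.** **The plan's own figure.** Section 4.4 says it can show an "increase or decrease in calcification score of 15%, in 4 subpopulations of 22 patients with ESRD". The test is two-sided at the 5% level and the power is 90%. The difference is 0.15 × 2370 = 355.5, with SD 352.

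- Formula as printed, with SD 352: 2 × (1.96 + 1.28)² × 352 / 355.5 = 20.8.
- Usual form, with the SD-to-difference ratio squared: 2 × (3.24)² × (352/355.5)² = 20.6, so 21.

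Both are close to the stated 22. The printed S = 3.52 would give 0.2 and is evidently a misprint of 352. This calculation concerns a 15% difference in score, not in progression, so it says nothing about the size of the present problem.

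**Inputs for the check**

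- Planned interval: 36 months (Section 3).
- Positive progression on dialysis: Section 10.4. Linear progression is my assumption.
- Share f of the analysed dialysis cohort with only a shortened change: not given. The Summary allows "to account for a 25% lost-to-follow-up-rate (e.g. by renal transplantation in the 3 dialysis groups, or by mortality". If x per 100 enrolled are transplanted with a closing scan and the other 25 − x are lost, then f = x / (75 + x), which is at most 25%. I use 10% and 25%.
- Exit times: not given. I take an even spread over 18–36 months (mean 27) if patients transplanted earlier contribute only to the transplant cohort, and over 6–36 months (mean 21) if they also contribute a dialysis change.

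**Understatement of mean dialysis progression:** u = f × (1 − mean exit time / 36).

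**Apparent reduction with transplantation when the true reduction is r:** 1 − (1 − r) / (1 − u).

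| Exits | f | u | True 15% appears as | True 30% appears as |
|---|---|---|---|---|
| 18–36 months | 10% | 0.10 × 0.250 = 2.5% | 1 − 0.85/0.975 = 12.8% | 28.2% |
| 18–36 months | 25% | 0.25 × 0.250 = 6.3% | 1 − 0.85/0.9375 = 9.3% | 25.3% |
| 6–36 months | 10% | 0.10 × 0.417 = 4.2% | 1 − 0.85/0.958 = 11.3% | 27.0% |
| 6–36 months | 25% | 0.25 × 0.417 = 10.4% | 1 − 0.85/0.896 = 5.1% | 21.9% |

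The 15% and 30% are illustrations, not planned effects. If every closing scan fell at the 18 months of Example 1, u would be f × 0.5, that is 5% or 12.5%.

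**Nocturnal versus conventional dialysis.** With equal f and equal timing, both means are multiplied by 1 − u. The relative difference is unchanged, and the absolute difference shrinks by the factor 1 − u. With unequal shares and exits at 18–36 months, take equal true progression. If f is 25% in nocturnal and 10% in conventional dialysis, nocturnal progression appears 1 − 0.9375/0.975 = 3.8% lower. With the shares exchanged it appears 0.975/0.9375 − 1 = 4.0% higher.

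**Noise of a per-year change.** Section 4.4 puts variation between measurements below 10%. Taking 10%, the measurement SD of an annualised change is 10% × √2 / t: 28.3% per year at t = 0.5 years, 9.4% at 1.5 and 4.7% at 3.

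**The case against.** The strongest reply is that pooling without adjustment is inferred. Section 7.4 openly acknowledges the shorter period, the hypothesis is worded as a rate, and a statistical analysis plan that is not shown could annualise the change or model time. This stands as a limit: the bias is conditional on the analysis being run as the protocol describes it. It does not remove the point, because the protocol itself assigns the shortened change to the primary endpoint and names analyses and adjustments without an interval.

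A reader might infer that the bias could reverse the transplant contrast. The documents do not support that. Reversal of a true 15% reduction appears, for example, with f = 45% and exits over 6–36 months: u = 0.45 × 0.417 = 18.8%, and 1 − 0.85/0.812 = −4.6%. The 45% comes from treating all 18 losses between 40 enrolled and 22 complete as transplant exits with scans. Section 4.4 names three other causes, and the Summary gives 25% for all causes together. The 6–36 month spread also sets aside the re-entry rule in 7.5.

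A reader might also infer that 4.4 and 7.4 contradict each other. They need not: a patient can be a dropout for sizing and still supply partial data. What is missing is a statement of whether such a patient counts towards the 22.

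Nor can one say that early exits fall into the lowest progression category. Section 9.1 gives no cut-points and does not say whether the categories are per year. On a raw change, a shorter interval only shifts patients towards lower categories.

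**Conclusion.** The point holds in conditional form. Followed as written, Sections 7.1.1, 7.4 and 9 place shortened changes beside 3-year changes, in the dialysis cohorts only. Given positive progression, dialysis progression is understated. A true advantage of transplantation over conventional hemodialysis or peritoneal dialysis is drawn towards no difference.

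For nocturnal versus conventional dialysis no direction can be claimed: equal transplant rates and timing leave the relative difference intact, and unequal ones can bias it either way.

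The size is illustrative. With linear progression and 10–25% early closing scans, the understatement is about 2.5–6% or 4–10%, depending on whether patients transplanted before 18 months contribute a dialysis change. Reversal of the contrast is not claimed. The matter should be corrected, since the distortion is systematic and the remedy is inexpensive.

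**What to change.** - **Sections 7.1.1 and 9.1–9.3:** define the primary outcome as the rate of change per year on the chosen transformed score. The preferred analysis is a mixed model of all scans (baseline, years 1 and 2, closing or year 3) on actual time since inclusion, with a cohort-by-time interaction. An additive interval term in a regression of raw change is no substitute, because it assumes one common slope when the cohort slopes are the question.
- **If a single change per patient is kept:** use annualised change weighted by its precision, which rises with interval length. Measurement error alone would imply weights in proportion to t²; true variation between patients makes the dependence weaker.
- **Section 9.1:** base the three progression categories on the per-year change.
- **Reporting:** give the number and median interval of early closing scans by cohort, and add a sensitivity analysis without them.
- **Section 4.4:** state whether patients with only a shortened interval count towards the 22.
- **Sections 7.4 and 7.5:** state whether patients transplanted at 6–18 months who re-enter the transplant cohort also contribute a dialysis-period change. Reconcile the general closing scan in 7.4 with the rule in 7.5 for transplants within 6 months.

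The cost is a few lines of text and no extra scans, since yearly CT is already planned. Actual scan dates must be captured, rates over short intervals are noisier, and the model assumes a linear course on the chosen scale.
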